Supplemental Digital Content

1. Study design and Setting:

The ELISPOT-TC trial will be a phase IV, multicenter, open-label, randomized (2:1) non-inferiority clinical trial conducted across 11 Spanish heart-transplant centers. The trial will evaluate a CMV-specific cellular immunity (CMI)-guided prevention strategy using the IFN-γ ELISpot (T-SPOT.CMV) assay versus standard universal valganciclovir prophylaxis for 3 months. Patients will be followed for 48 weeks after transplantation.

1. Study Objectives and Endpoints:

The primary objective of the ELISPOT-TC trial will be to estimate and compare the cumulative incidence of cytomegalovirus (CMV) infection during the first year after heart transplantation among CMV-seropositive (IgG-positive) recipients assigned to either a CMI-guided prevention strategy or standard universal valganciclovir prophylaxis.

The primary endpoint will be the cumulative incidence of CMV infection at one year post-transplant. CMV infection will be categorized as clinically significant or non-significant according to predefined standardized thresholds agreed upon across centers:

Clinically significant CMV infection will be defined as CMV DNAemia ≥ 1000 IU/mL or ≥ 500 copies/mL in plasma, or ≥ 4500 IU/mL or ≥ 3000 copies/mL in whole blood, or any detectable viral replication associated with CMV syndrome or tissue-invasive disease.

Non-significant CMV infection will include episodes of CMV DNAemia below these thresholds without clinical manifestations.

Secondary endpoints will include the incidence of CMV disease, acute graft rejection, opportunistic infections, hematologic adverse events, all-cause mortality, and cost-effectiveness of both preventive strategies.

1. Participants:

Eligible participants will be adult (≥18 years) CMV-seropositive (IgG-positive) heart transplant recipients of either sex. Written informed consent will be obtained before inclusion. Exclusion criteria will include pregnancy or lactation, administration of thymoglobulin as induction therapy, or any contraindication to receive ganciclovir or valganciclovir. Fertile women will be required to use effective contraception for at least 30 days after treatment, and men for 90 days unless the partner is not at risk of pregnancy.

1. Randomization and Allocation Concealment:

Participants will be randomized using a centralized computer-generated system in a 2:1 ratio (experimental:control), stratified by center. The allocation sequence will be generated electronically by the coordinating center and implemented via a secure web-based platform to ensure concealment. Due to the nature of the interventions, masking of investigators and participants will not be feasible.

1. Interventions:

*Assessment of CMV-specific Cell Mediated Immunity:*

The commercially available IFN-γ ELISpot assay T-SPOT®.CMV (Oxford Immunotec, ltd., Oxford, UK) will be used to assess the CMI against 2 major immunogenic CMV antigens (IE-1 and pp65) using overlapping peptide

pools covering the whole antigen length and has been conducted following manufacturer guidelines. Briefly, 2.5x10^5^ PBMC (in 100µl) will be stimulated with CMV antigens for 20 hours in duplicate wells. IFN-ɣ spots will be detected after using biotinylated anti-human IFN-ɣ antibody plus the addition of alkaline phosphatase conjugate substrate. IFN-ɣ spots obtained will be counted with an ELISPOT reader (AID® Gmbh, ELISPOT Reader HR fourth generation). In each test, AIM-V medium alone and Phytohemagluttinin (PHA) will be used as negative and positive controls, respectively. Total CMV-specific IFN-ɣ spots will be provided after subtracting the number of IFN-ɣ spots observed in the respective negative controls.

The cut-offs that will be used for decision-making are as follows:

**Low CMV risk:** >40 IFN-γ spots/2.5 x10^5^ for IE-1 antigen and >170 IFN-γ spots/2.5 x10^5^ for pp65 antigen

**High risk:** <40 IFN-γ spots/2.5 x10^5^ for IE-1 antigen and <170 IFN-γ spots/2.5 x10^5^ for pp65 antigen or IE-1<40 and pp65>170 or IE-1>40 and pp65<170

**Unreactive:** <5 IFN-γ spots/2.5 x10^5^ for IE-1 antigen and <5 IFN-γ spots/2,5 x10^5^ for pp65 antigen and positive control with 5-50 IFN-γ spots/2.5 x10^5^ for both antigens.

Samples yielding an undetermined T-SPOT.CMV result will be repeated. Samples classified as unreactive will be considered high-risk.

Only 10-days post-transplant IFN-γ T-SPOT.CMV assays will be performed using fresh peripheral blood samples in group 1 in order to stratify patients, whereas pre-transplant, 10 days post-transplant from group 2 and end of treatment (three months) immune assays will be performed using frozen samples, isolated and cryopreserved in liquid nitrogen for its subsequent evaluation at the end of the trial.

Samples will arrive at the laboratory within 24 hours after extraction and will be processed within 32 hours with the T-cell Extend® reagent. This reagent is an antibody complex that is added to blood samples in the laboratory immediately before running the T-SPOT.TB assay and allows blood samples to be processed up to 32 hours after venepuncture without affecting the accuracy of the test.

*CMV Serology and Microbiological studies:*

Pre-transplant CMV serological status of all donor and recipients will be determined using a Human Anti-CMV IgG Enzyme-Linked ImmunoSorbent Assay (ELISA) kit in each center.

Surveillance of CMV DNAemia will be performed with real-time polymerase

chain reaction kit in plasma or whole blood in each center laboratory. Results will be despicted as IU/mL or copies/mL. CMV DNAemia will be considered positive when detectable above 1000 IU / mL or 500 copies / mL in plasma or above 4500 IU / mL or 3000 copies / mL in whole blood.

*CMV Preventive strategies:*

Patients randomized at ELISPOT group (group 1) will be stratified based on the result of the IFN-γ T-SPOT.CMV assays into high risk of developing CMV infection or low risk of developing CMV infection.

Those patients classified as high risk for developing CMV infection (group 1 a) due to a high risk, undetermined or unreactive result will receive **universal prophylaxis** with valganciclovir 900 mg / 24h for 3 months (and adjusted to the glomerular filtrate rate of the patient). In case prophylaxis can’t be done orally, intravenous ganciclovir will be used at 5-10 mg / kg / day for 1-3 months.

In these patients, treatment will begin once the result is obtained, between days 10 and 15 post-transplant, taking into account that there is a window of 10 +/-2 days for extraction of the sample, which will be received in 24-36 hours in the central laboratory, obtaining the result 48 hours after the extraction. If the sample is not valid, the extraction and determination can be repeated, as long as it allows prophylaxis to begin at the latest on day 15 post-transplant, so as not to increase the risk of CMV infection.

Patients randomized to control group (group 2) will receive **universal prophylaxis** with valganciclovir 900 mg / 24h for 3 months (and adjusted to the glomerular filtrate rate of the patient). In case prophylaxis can’t be done orally, intravenous ganciclovir will be used at 5-10 mg / kg / day for 1-3 months. Prophylaxis can be started after sample extraction (day 10 +/- 2 days post-HT) and no later than day 15 post-HT, therefore maintaining the same window period to start prophylaxis in both groups (group 1a and control group).

*Surveillance of CMV:*

After stopping prophylaxis in both groups, patients will be followed preemptively with CMV Quantitative Nucleic Acid Testing (QNAT) every month until month 6 and at month 12 after transplantation.

Patients randomized to the intervention group who present a low-risk T-SPOT.CMV result (group 1b) will follow a **preemptive therapy**, consisting in weekly QNAT during the first month, every two weeks until month 3, monthly until month 6 and at month 12 after transplantation. Antiviral treatment will be initiated in those patients with a DNAemia above ≥1000 IU / mL or ≥500 copies / mL in plasma (or ≥4500 IU / mL or ≥3000 copies / mL in whole blood) without associated symptoms or the presence of any level of replication with associated viral syndrome or CMV disease, ultimately being at the discretion of the attending physician. Patients will be treated with valganciclovir 900 mg / 12 h or ganciclovir 5 mg / kg every 12 hours (adjusted according to renal function and possible adverse events, at the discretion of the attending physician), a minimum of 14 days in case of asymptomatic DNAemia or a minimum of 21 days in case of CMV viral syndrome o CMV disease. If patients cannot receive valganciclovir or ganciclovir, other antivirals are allowed. To stop treatment, 2 negative viral load results must be obtained in 2 consecutive determinations obtained at least 1 week apart.

QNAT will be performed on all patients at the time of sample extraction for IFN-γ T-SPOT.CMV assay (10 +/-2 days post-HT and three months after trasplantation).

If DNAemia is detected in either of the two groups that will need prophylaxis, before starting it, they will continue to be eligible for prophylaxis as long as they do not exceed the following cut-off points that we have considered to be clinically significant (as explained below).

QNAT will also be performed on all patients at discharge, at 3 months (12 ± 4 weeks), 4 months (16 ± 4 weeks), 5 months (20 ± 4 weeks), 6 months (24 ± 4 weeks) and one year (48 ± 4 weeks) post-HT in the local laboratories of each center.

In patients receiving prophylaxis (group 1 a and control group) QNAT will be also performed at 15 days (± 3 days) after the end of treatment.

Although no clinical guidance has been provided on the treatment of late disease, the treatment received will be recorded.

1. Sample Size Calculation and Statistical Analysis:

Sample size will be dtermined assuming a 40% cumulative incidence of CMV infection at one year, a one-sided type I error of 2.5%, 80% statistical power, and a 10% non-inferiority margin. A total of 188 patients (125 experimental and 63 control) will be required, accounting for an anticipated 10% dropout rate. Analyses will be conducted on both an intention-to-treat and per-protocol basis. Comparisons between groups will use standard parametric or nonparametric tests as appropriate. Time-to-event analyses will be performed using Cox proportional hazards models and Kaplan–Meier survival curves. Cost-effectiveness analyses will include both direct and indirect healthcare costs. All statistical tests will be two-sided, and p-values <0.05 will be considered significant.

1. Ethical Approval:

The trial will comply with the Declaration of Helsinki and Spanish legislation. Approval has been obtained from the national regulatory authority and all local ethics committees at participating centers. All patients will provide informed consent before any study procedure. The study has been registered at ClinicalTrials.gov (NCT04278547).

1. Funding:

This work will be supported by the Instituto de Salud Carlos III (Grant number PI19/01610), co-founded by the Spanish Cardiology Society (Grant number 19PSJ017) and by the Spanish Platform for Clinical Research and Clinical Trials, SCReN (Spanish Clinical Research Network), financed by the ISCIII-General Subdirectorate of Evaluation and Promotion of Research, through project PT17/0017/0010 and PT20/00008 integrated into the I+D+I 2013-2016 State Plan and co-financed by the European Regional Development Fund (FEDER). We thank *CERCA Programme / Generalitat de Catalunya* for institutional support.

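### The 188 patients do not follow from the printed inputs: with 40% in both arms and a 10-point absolute margin, 188 gives about 24% power, and 80% would need about 944

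*Protocol*

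**What the plan says.** Protocol, Sample Size Calculation and Statistical Analysis, gives one event rate, "assuming a 40% cumulative incidence of CMV infection at one year", and sets "a one-sided type I error of 2.5%, 80% statistical power, and a 10% non-inferiority margin". It concludes: "A total of 188 patients (125 experimental and 63 control) will be required, accounting for an anticipated 10% dropout rate".

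Protocol, Randomization and Allocation Concealment, fixes the allocation "in a 2:1 ratio (experimental:control), stratified by center". Study design and Setting describes a randomized non-inferiority trial, and Study Objectives and Endpoints makes one-year cumulative incidence of CMV infection the primary endpoint.

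The protocol does not say whether the 40% applies to one arm or both, whether the 10% margin is absolute or relative, or which formula was used.

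**The concern.** The paragraph prints nearly everything needed to recompute the sample size, and the total looks far too small. Excluding a 10-point difference when events occur in 40% of patients takes several hundred patients, and only about 170 of the 188 would remain after the stated dropout.

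The stated power tells readers how often the trial would fail if the two strategies were equally good. They are told one time in five. If the true figure is nearer three in four, a failure to show non-inferiority would be the expected result even with equal strategies, and it could be misread as evidence against the guided strategy.

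**Working it through.** **Inputs.** From the sample-size section: incidence 0.40, one-sided alpha 0.025 (z = 1.960), power 0.80 (z = 0.842), margin 0.10, dropout 10%, total 188 = 125 + 63. From the randomization section: allocation 2:1.

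**Assumptions, not stated in the protocol.** 40% applies to both arms, and the margin is an absolute difference of 10 points.

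**1. Attempt to reproduce 188.** Two-arm non-inferiority, normal approximation with unpooled variance, ratio r = 2:

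n_control = (z_alpha + z_beta)² × [p(1−p) + p(1−p)/r] / margin²

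= 7.849 × [0.24 + 0.12] / 0.01 = 282.6, so 283.

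n_experimental = 2 × 283 = 566. Total evaluable = 849. With dropout: 849/0.9 = 943.3, so 944.

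The stated 188 is about one fifth of this and is not reproduced.

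**2. Variants, keeping 40% in both arms and a 10-point margin.**

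| Change | Total randomized |
|---|---|
| One-sided alpha 5% | 744 |
| One-sided alpha 10% | about 544 |
| 1:1 allocation | 838 |
| Dropout added as N × 1.1 | 934 |
| Hazard-ratio scale (40% v 50%) | about 1,056 |

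None is near 188. Reading the margin as relative (10% of 40% = 4 points) makes the shortfall larger.

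**3. Power of 188.** After 10% dropout, about 57 control and 113 experimental patients are evaluable.

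SE = √[0.24 × (1/57 + 1/113)] = 0.0796.

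Power = Φ(0.10/0.0796 − 1.960) = Φ(−0.70) = 0.24. Simulation with 400,000 runs gives 0.241.

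With no dropout (63/125): SE = 0.0757 and power = 0.26 (simulation 0.262).

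**4. Precision.** The expected 95% CI half-width at 57/113 is 1.96 × 0.0796 = 0.156, about 16 points, which is wider than the margin. At about 40% in both arms, the upper limit falls below 10 points only if the observed incidence is at least about 5.6 points lower in the guided arm (0.100 − 0.156 = −0.056).

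**5. Sensitivity to the unstated experimental rate.** Control 40%, 10-point margin, one-sided 2.5%, 57/113 evaluable:

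| Experimental rate | Power |
|---|---|
| 40% | 24% |
| 35% | 48% |
| 30% | 73% |
| 28% | 81% |

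**6. Routes that do give 188.**

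- One-sample formula on the printed rate, alpha, power and margin: 0.24 × 7.85 / 0.01 = 188.4. A total of 188 splits 2:1 into 125 + 63. There is no two-arm variance and no dropout allowance.
- Common incidence 5%, other inputs as printed: 55.9, so 56 + 112 evaluable. Dividing each arm by 0.9 gives 63 + 125.
- Control 40%, experimental 28%: 56 + 112, then 63 + 125.
- 40% in both arms with a margin of about 22.5 points: 56 + 112, then 63 + 125.
- 40% in both arms, 20-point margin, one-sided 5%: 55.6, so 56 + 112, then 63 + 125.

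**The case against.** The strongest objection is that the protocol never says 40% holds in both arms. If the planners expected the guided strategy to lower incidence to about 28%, 188 patients would give about 80% power and the arithmetic would be sound. This stands to the extent that the 24% is conditional on equal rates and should be labelled so. It does not rescue the paragraph. A 12-point benefit would be the most influential input in the calculation, and it is not printed; power falls to 73% at 30% and 48% at 35%.

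A reader might also infer that some input behind 188 must differ from the one printed. The document does not support that. The printed rate, alpha, power and margin, put into a one-sample formula, give 188.4. The inputs may therefore all be as printed and the formula wrong, in which case the claim of "accounting for an anticipated 10% dropout rate" would also be untrue. Several sets of changed inputs fit equally well, so the origin cannot be settled from the protocol.

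Finally, one could argue that if 188 came from a wider margin or a larger alpha, the sponsor need only print those values. That would fit the criterion for success to the sample size. It would also depart from the one-sided 2.5% in the same paragraph, and nothing in the protocol justifies a 20-point margin on a 40% rate.

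**Conclusion.** The point holds. The stated 188 does not deliver the stated 80% power under any standard two-arm, 2:1 non-inferiority calculation with the printed inputs. Assuming 40% in both arms and an absolute 10-point margin, about 944 randomized patients are needed, and 188 gives about 24% power after dropout (26% with none). If the strategies are truly equal, the trial would then fail to show non-inferiority about three times in four.

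The size of the shortfall depends on those two assumptions. A lower experimental rate reduces it, and a relative margin enlarges it. How 188 was obtained is not established.

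**What to change.** Correct the sample-size paragraph:

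- State the incidence assumed in each arm, whether the margin is absolute or relative, and the formula used.
- If 40% in both arms, 10 absolute points and one-sided 2.5% stand, restate the power of 188 patients as about 24% and give the expected 95% CI half-width of about 16 points.
- If a lower experimental rate was assumed, state it, justify it, and show power across a range of rates such as that in step 5 of the working.
- Do not widen the margin or alpha to fit 188.
- If no inflation for dropout was applied, remove the statement that it was.

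These are changes of protocol wording. The cost is a less favourable stated power. Keeping 80% power with the inputs on the ordinary reading would instead take about 944 patients.

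### No baseline covariate is named for the group comparison, although donor CMV serostatus and a pre-transplant T-SPOT.CMV result are collected; an adjusted risk difference would cost little and gain a modest, uncertain amount of precision

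*Protocol*

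**What the plan says.** The analysis paragraph (Protocol, Sample Size Calculation and Statistical Analysis) states: "Comparisons between groups will use standard parametric or nonparametric tests as appropriate". It then lists Cox models and Kaplan-Meier curves for time-to-event analyses. No covariate or stratification factor is named for any of these, and no method is tied explicitly to the primary endpoint.

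Two baseline measurements that bear on CMV risk are planned:

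- Donor serostatus (Interventions, CMV Serology and Microbiological studies): "Pre-transplant CMV serological status of all donor and recipients will be determined".
- Pre-transplant cellular immunity (Interventions, Assessment of CMV-specific Cell Mediated Immunity): "pre-transplant, 10 days post-transplant from group 2 and end of treatment (three months) immune assays will be performed using frozen samples". Only the day-10 assay in group 1 is run fresh, so the natural reading is that the pre-transplant assay is done on frozen cells in both arms.

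Randomisation is 2:1 and stratified by center only (Randomization and Allocation Concealment). The sample size rests on "assuming a 40% cumulative incidence of CMV infection at one year", with "a one-sided type I error of 2.5%, 80% statistical power, and a 10% non-inferiority margin".

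**The concern.** The trial is built on the idea that CMV-specific cellular immunity sorts patients by risk of CMV infection: IE-1 and pp65 counts decide who is labelled low or high risk in the experimental arm. The same assay taken before transplantation, and the donor's serostatus, precede any difference in strategy, so both are legitimate baseline covariates. Neither is balanced by the randomisation and neither is used in the stated analysis.

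If these variables predict one-year infection, a comparison without them leaves explainable outcome variation in the standard error, and the confidence interval set against the 10-point margin is wider than it needs to be. With 63 controls planned, unused precision is worth recovering. The trial is open-label, so covariates chosen after the data have been seen would be open to challenge; they are best fixed beforehand.

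**Working it through.** **Inputs from the protocol.** One-year incidence 40% (one rate is given; read as equal in both arms); one-sided type I error 2.5%; power 80%; margin 10% (scale not stated; read as an absolute risk difference); 125 experimental and 63 control; 10% dropout. Evaluable after dropout: 125 × 0.9 = 112.5 and 63 × 0.9 = 56.7.

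**Assumed.** R², the share of outcome variance that the covariates explain. The document gives no figure, so a range is shown.

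**Step 1: the plan's own figure.** Controls needed = (1.960 + 0.842)² × (0.24 + 0.24/2) / 0.10² = 282.6, rounded up to 283. With 566 experimental the total is 849 evaluable, and 849/0.9 = 943.3, so 944 randomised. The protocol says: "A total of 188 patients (125 experimental and 63 control) will be required, accounting for an anticipated 10% dropout rate". The stated inputs do not reproduce 188. That is a separate matter, but it sets the base from which any gain is measured.

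**Step 2: precision without covariates.** SE = √[0.24 × (1/112.5 + 1/56.7)] = 0.0798. The 95% half-width is 1.96 × 0.0798 = 15.6 points. Power = Φ(0.10/0.0798 − 1.96) = 24.0%. With 125 v 63 and no dropout, SE = 0.0757, half-width 14.8 points and power 26%.

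**Step 3: precision with adjustment.** Multiply the variance by (1 − R²). For a two-level covariate with share f and risk gap d, R² = f(1 − f)d²/0.24. With f = 0.5 assumed, d of 20, 30 and 40 points gives R² of 0.042, 0.094 and 0.167.

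| Assumed R² | SE (112.5 v 56.7) | 95% half-width, points | Power | Gain, points |
|---|---|---|---|---|
| 0 | 0.0798 | 15.6 | 24.0% | – |
| 0.02 | 0.0790 | 15.5 | 24.4% | 0.4 |
| 0.042 | 0.0781 | 15.3 | 24.8% | 0.8 |
| 0.094 | 0.0760 | 14.9 | 26.0% | 2.0 |
| 0.167 | 0.0728 | 14.3 | 27.9% | 3.9 |
| 0.25 (correlation 0.5) | 0.0691 | 13.5 | 30.4% | 6.4 |

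With 125 v 63, R² of 0.02, 0.094 and 0.167 takes power from 26.1% to 26.6%, 28.4% and 30.4%. Donor serostatus alone, with an assumed donor-positive share of 50% to 80% and a risk gap of 10 to 30 points, gives R² of only about 0.01 to 0.09.

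**Step 4: chance imbalance.** For a 50/50 class, the 95% range of the difference in share between arms is 1.96 × √[0.25 × (1/112.5 + 1/56.7)] = ±16 points. Multiplied by d of 20, 30 or 40 points, this moves the estimated risk difference by up to ±3.2, ±4.8 or ±6.4 points. This is not an additional loss. At d = 40 points its variance is 0.40² × 0.25 × 0.02653 = 0.00106, against a total of 0.24 × 0.02653 = 0.00637: 17%, the same share counted in Step 3.

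**Step 5: can adjustment rescue the design?** For 112.5 v 56.7 patients to reach 80% power, R² would have to be about 0.8. That is far outside the range considered here.

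**The case against.** The strongest reply is that the protocol has not fixed anything wrong. The sentence on tests is generic and covers all comparisons; the word unadjusted does not appear; the Cox models named next can carry covariates; and a covariate list is often left to the SAP, which is not shown. This stands in part. A reader might infer that the protocol commits the primary analysis to an unadjusted two-group test, and the text does not support that. What remains is that the method it does state contains no baseline covariate, and that a better one is available from data already being collected.

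A reader might also infer that chance imbalance biases the result. It does not: under randomisation the unadjusted difference is valid, and its interval already covers such imbalance, as Step 4 shows.

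The assumed gains may also be optimistic. The protocol assigns risk from the day-10 result and does not say that the pre-transplant count or donor serostatus predicts infection in seropositive recipients. In the experimental arm, prophylaxis goes to the high-risk class and preemptive monitoring to the low-risk class. If prophylaxis works, that weakens, or could even reverse, the link between immunity and infection in two thirds of the patients. This stands in full. It reduces the expected size of the gain but is no reason to leave out the covariates.

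**Conclusion.** The point holds as a low-cost improvement, not as an error that invalidates the analysis. The protocol collects two plausible baseline predictors, balances neither and names neither in its comparison. For an assumed variance reduction of 2% to 17%, the gain is about 0.5 to 4 power points from a base of about 24% to 26%, and the half-width narrows by roughly 0.2 to 1.4 points. These figures rest on 40% in both arms, an absolute 10-point margin, a common R² in both arms and predictive strengths that the document does not supply. Treatment by risk class may make the true gain smaller.

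A gain above 5 points, or a move from a nominal 80% to about 90%, should not be claimed. The first needs a correlation near 0.5 with the outcome, for which the document gives no support. The second describes a design with 80% power, which the planned numbers do not deliver on the stated inputs.

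**What to change.** Pre-specify the primary one-year risk difference as a marginal estimate, obtained by standardisation (g-computation) from a logistic model with arm, donor CMV serostatus and the pre-transplant IE-1 and pp65 spot counts. The result then stays on the risk-difference scale and can be compared directly with the 10-point margin.

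- Enter each count as log(count + 1). Counts are reported after subtracting the negative control, so set any negative value to 0 first.
- Use a missing-indicator for absent or invalid pre-transplant assays, so that no patient is dropped.
- Report the unadjusted difference as a sensitivity analysis.
- Do not adjust for the day-10 assay: it is fresh in group 1 and frozen in group 2, so the two arms' values are not measured alike.

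The cost is analysis-plan wording and some programming, with no extra patients, visits or assays. The downside is that the adjusted result must wait for the frozen assays, already planned for the end of the trial, and some may be missing or fail. The gap between 188 and the number implied by the stated inputs needs its own resolution; adjustment does not close it.

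### Randomisation is stratified by center, but the analysis paragraph does not carry center into the comparison: a small, cheap gain in precision

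*Protocol*

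**What the plan says.** Under *Randomization and Allocation Concealment* the Protocol states: "Participants will be randomized using a centralized computer-generated system in a 2:1 ratio (experimental:control), stratified by center". *Study design and Setting* says that the trial is "conducted across 11 Spanish heart-transplant centers".

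Virology is local. Under *CMV Serology and Microbiological studies*, DNAemia is measured with a real-time polymerase "chain reaction kit in plasma or whole blood in each center laboratory", and "Results will be despicted as IU/mL or copies/mL". *Study Objectives and Endpoints* classifies infections as clinically significant or not by "predefined standardized thresholds agreed upon across centers".

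The analysis text is in *Sample Size Calculation and Statistical Analysis*: "Comparisons between groups will use standard parametric or nonparametric tests as appropriate", and "Time-to-event analyses will be performed using Cox proportional hazards models and Kaplan–Meier survival curves". That paragraph does not mention center. It does not say that the comparison will be stratified or adjusted by center, and it does not say that it will not be.

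**The concern.** Stratified randomisation balances the arms within each center. When centers differ in incidence, this removes between-center variation from the true sampling error of the treatment difference. An ordinary two-sample formula does not know this and still counts that variation as noise. The reported standard error is then larger than the true one, the interval is wider than it needs to be, and the non-inferiority test is conservative.

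Followed literally, the analysis paragraph gives that ordinary two-sample comparison. Centers could well differ here, because each laboratory uses its own kit and results come from different specimens and in different units. At stake is some precision that the design has already secured, in a trial that has little to spare for a 10-point margin.

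**Working it through.** **Inputs from the Protocol.** 11 centers; 2:1 allocation stratified by center; 188 patients (125 + 63), including 10% dropout; one-year incidence 40%, one-sided alpha 2.5%, power 80%, margin 10%. I take the margin as absolute percentage points. Average center size is 188/11 ≈ 17 patients, of whom 63/11 ≈ 6 are controls.

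**Assumed.** The Protocol gives no between-center variation. I express it as an ICC, the share of outcome variance that lies between centers, and vary it from 0 to 0.20.

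**The plan's own figure.** Controls needed = 0.24 × (1 + 1/2) × (1.960 + 0.842)² / 0.10² ≈ 283. With 566 experimental patients the total is 849, and 849/0.9 gives 944 with dropout. The stated inputs do not give 188. That is a separate problem; it matters here only because it sets the power level at which the gain is judged.

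**Analysis that ignores center.** SE = √(0.24/125 + 0.24/63) = 0.0757. The 95% half-width is 1.96 × 0.0757 = 14.8 points. Power = Φ(0.10/0.0757 − 1.96) = 26.1%.

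**Analysis stratified by center.** Replace 0.24 by 0.24 × (1 − ICC):

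| Assumed ICC | SE | Half-width (points) | Power |
|---|---|---|---|
| 0 | 0.0757 | 14.8 | 26.1% |
| 0.02 | 0.0749 | 14.7 | 26.6% |
| 0.05 | 0.0738 | 14.5 | 27.3% |
| 0.10 | 0.0718 | 14.1 | 28.5% |
| 0.20 | 0.0677 | 13.3 | 31.5% |

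With about 170 evaluable patients (113 + 57), power goes from 24.1% at ICC 0 to 28.9% at ICC 0.20.

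**What these ICCs mean.** Eleven incidences spread evenly over a range R have variance R²/10. A spread of 25–55% gives 0.009/0.24 ≈ 0.04; 20–60% gives 0.016/0.24 ≈ 0.07; 15–65% gives 0.025/0.24 ≈ 0.10. The interval narrows by 2% to 5% over these three cases. An ICC of 0.20 needs R = √(10 × 0.048) ≈ 0.69, roughly 5% to 75%, so the last row of the table describes very large differences between centers.

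**Check by simulation.** 11 centers, 188 patients, permuted blocks of 3 within center (assumed), no treatment effect, 4000 runs. The unstratified Wald interval is compared with the Mantel-Haenszel risk difference using the Sato variance:

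| ICC | True SD of estimate (either method) | Reported SE, unstratified / stratified | Power | Coverage |
|---|---|---|---|---|
| 0 | 0.075 | 0.0753 / 0.0754 | 25.2% / 25.3% | 94.7% / 94.6% |
| 0.036 | 0.075 | 0.0752 / 0.0740 | 24.7% / 26.1% | 95.4% / 95.0% |
| 0.09 | 0.073 | 0.0750 / 0.0719 | 25.1% / 28.4% | 95.3% / 94.2% |
| 0.17 | 0.069 | 0.0747 / 0.0686 | 24.6% / 30.6% | 96.3% / 94.5% |

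The estimate itself varies by the same amount under both methods; what changes is the reported SE. The Monte Carlo error on coverage is √(0.95 × 0.05/4000) ≈ 0.3 points, so the shortfall of the stratified interval is slight.

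**The case against.** The strongest objection is that a reader might infer that the Protocol plans an unstratified analysis. It does not say so. Generic tests and Cox models leave room for stratification by center, and this detail is often left to a statistical analysis plan, which is not at hand here. That stands: the point cannot be put as an error or a contradiction. What remains is that the analysis text, followed as written, does not use the factor used for randomisation, and that using it is better at almost no cost.

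Second, the gain rests on an unknown. At ICC 0 there is none. This also stands, which is why only a range is given.

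Third, a reader might infer from the local assays that the comparison is biased, or that center fixes who counts as an event. The documents do not support either. Allocation is balanced within center, so assay differences fall on both arms alike, and common cut-offs are set for each specimen and unit. The Protocol does not say that each center keeps to one specimen and one unit. *Study Objectives and Endpoints* also counts DNAemia below the cut-offs as infection of the non-significant kind, although the microbiology section calls DNAemia positive only above them. Local assays make differences between centers plausible, and no more than that.

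Finally, ignoring center errs on the safe side: it does not raise the risk of a false non-inferiority claim.

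**Conclusion.** The point holds as a minor gain in precision. Under a 40% incidence in both arms, a 10-point absolute margin and 125 + 63 patients, stratifying by center raises power from about 26% by 0 to 5 points for an assumed ICC of 0 to 0.20. The upper end requires very large differences between centers.

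A reader might hope that this makes the trial adequate for its margin. It does not. Even with stratification, the stated inputs need 681 to 849 patients (757 to 944 with dropout) over the same ICC range, against 188 planned.

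**What to change.** Add one sentence to the analysis paragraph: the primary difference in one-year incidence of CMV infection is estimated stratified by center, for example as a Mantel-Haenszel risk difference with a sparse-strata (Sato) variance, and the Cox model is stratified by center. If a statistical analysis plan already says this, a cross-reference is enough. Donor CMV serostatus, which is determined before transplant, may be added to a supporting model; that is optional.

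No extra data are needed. There are two small costs. Coverage may fall slightly below nominal with about 17 patients per center (94.2% to 94.5% at the two larger simulated ICCs). A center with patients in only one arm contributes nothing to the Mantel-Haenszel estimate, so a rule for pooling very small centers should be fixed before the outcome data are seen.
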